## Abstract

[^177^Lu]Lu-PSMA-617 radiopharmaceutical therapy has been approved for the treatment of men with metastatic castration-resistant prostate cancer (mCRPC) using a fixed dosing schedule of once every 6 wk for up to a total of 6 doses. We hypothesized that patients may benefit from a flexible and extended dosing schedule, up to 12 doses with potential “treatment holiday” periods. **Objective:** The objective of this study is to determine the 2-y survival rate of patients with mCRPC treated with an extended and flexible dosing schedule of [^177^Lu]Lu-PSMA-617 therapy in comparison to patients treated with the standard fixed dosing schedule of a maximum of 6 treatment cycles once every 6 wk. **Study Design:** The FLEX-MRT trial is an investigator-initiated prospective phase 2, parallel group, randomized, controlled, open-label, single-center trial in men with mCRPC to determine the efficacy of a flexible and extended dosing schedule of [^177^Lu]Lu-PSMA-617 therapy. Key inclusion criteria are patients eligible for Pluvicto (i.e., prior androgen receptor signaling inhibitors, prior chemotherapy, PSMA PET VISION criteria). Key exclusion criteria are prior [^177^Lu]Lu-PSMA-617 therapy and less than 6 wk since last myelosuppressive therapy. The trial aims to centrally randomize 90 patients in a 1:1 ratio to 2 treatment arms. In the control arm, patients will be treated with the approved standard dosing schedule (*n* = 45). In the investigational arm, patients will be treated with up to 12 cycles and with potential treatment holidays depending on response (*n* = 45). Response assessment is based on SPECT/CT at each cycle and on PSMA PET/CT during treatment holiday periods (every 12 wk). Primary endpoint is the 2-y survival rate. Survival is calculated from the date of the first cycle of [^177^Lu]Lu-PSMA-617 therapy. Secondary endpoints include safety by Common Terminology Criteria for Adverse Events and dosimetry and determination of overall and progression-free survival (evidence of progression as defined by radiographic, prostate-specific antigen level, or clinical progression, or death from any cause).

Radiopharmaceutical therapy (RPT) with [^177^Lu]Lu-PSMA-617 was approved both by the U.S. Food and Drug Administration and the European Medicines Agency in 2022 for the treatment of patients with metastatic castration-resistant prostate cancer (mCRPC) following the VISION trial (1,2). The VISION trial demonstrated that ^177^Lu-PSMA RPT can improve overall survival, radiographic progression-free survival (PFS), prostate-specific antigen (PSA) response, quality of life, and bone pain in patients with progressing mCRPC in comparison to the standard of care (2,3). However, even after a good response to [^177^Lu]Lu-PSMA-617 therapy, patients will eventually relapse and further treatment opportunities are limited. Hence, further optimization of the treatment is warranted.

Following the VISION trial design, [^177^Lu]Lu-PSMA-617 was approved by the Food and Drug Administration for patients with mCRPC on a fixed dosing schedule: up to 6 doses (cycles) of [^177^Lu]Lu-PSMA-617 at an injected activity of 7.4 GBq, administered at a time interval of 6 wk.

Retreatment (after an interval without ^177^Lu-PSMA, with or without other therapy) and extended regimen (>6 cycles) of ^177^Lu-PSMA therapy have been performed successfully outside of the United States with favorable efficacy and toxicity profiles (4–9). There are no guidelines for the optimum number of cycles of ^177^Lu-PSMA in patients who show good response. Because of the approved drug label and insurance coverage, ^177^Lu-PSMA is usually discontinued after a maximum number of 6 cycles. Moreover, some patients experience a complete or almost complete response (CR) before the last cycle 6 (e.g., after cycle 2). It is unclear whether these patients benefit from the subsequent remaining treatment cycles. In these patients with no visible lesions anymore on PET or SPECT or with limited or minimal residual lesions, the risk–benefit ratio may not be in favor of administering the subsequent treatment cycles. ^177^Lu-PSMA therapy may be saved for later time points, when the disease becomes again visible and large enough to be treated with β-radiation. A treatment holiday could reduce patients’ exposure to the therapy and prevent unnecessary toxicity when treatment seems to be already maximally effective, with potentially no further benefit expected from further treatment cycles. The concept of treatment holidays in patients experiencing a complete or almost CR before the last cycle 6 (e.g., after cycle 2) has been reported by Emmett et al. and Seifert et al. (7,10).

In the randomized phase 2 trial FLEX-MRT (ClinicalTrials.gov identifier: NCT06216249), we aimed at assessing prospectively the concept of a flexible and extended (>6 cycles) regimen of ^177^Lu-PSMA RPT that includes potential treatment holiday periods, and up to 12 cycles.

## MATERIALS AND METHODS

The full study protocol and the SPIRIT guidelines checklist are provided as supplemental materials (available at http://jnm.snmjournals.org) (11).

## STUDY DESIGN

### Overall Study Design

This is a prospective, open-label, randomized, controlled, parallel group, single-center phase 2 trial of a flexible and extended dosing schedule of [^177^Lu]Lu-PSMA-617 therapy in comparison to the standard fixed dosing schedule in patients with mCRPC.

The study was powered to demonstrate a survival benefit of the flexible and extended dosing schedule in comparison to the standard fixed dosing schedule. We hypothesized a 2-y survival rate of 55% in the investigational group and 30% in the control group (2). The overall sample size is 90 patients (45 in the control group and 45 in the treatment group) to achieve 80% power. The planned study duration is 48 mo.

The flexible dosing schedule in the investigational arm will be based on SPECT/CT response assessments obtained 24 h after the injection of [^177^Lu]Lu-PSMA-617. The response assessment during treatment holiday periods will be based on prostate-specific membrane antigen (PSMA) PET/CT every 12 wk using RECIP guidelines.

Single-time-point SPECT/CT dosimetry protocol at every cycle will be performed and will allow the number of cycles that subjects may receive under the study without exceeding the kidney dose threshold to be determined. An interim safety analysis with a stopping rule based on safety outcomes is planned at 50% of enrollment.

The overall study design is shown in Figure 1.

**FIGURE 1. fig1:**
[figure not shown]
Study design. FLEX-MRT trial will randomize 90 patients in 1:1 ratio to investigational arm treated with extended and flexible dosing schedule and control arm treated with approved standard dosing schedule. Primary endpoint is 2-y survival rate. ARSI = androgen receptor signaling inhibitor; CTx = chemotherapy; QOL = quality of life.

### Trial Registration

The FLEX-MRT trial is taking place at the Ahmanson Translational Theranostics Division at the University of California Los Angeles (UCLA). FLEX-MRT is an investigator-initiated trial supported by Novartis, conducted under the Investigational New Drug Application 168362 and approved by the UCLA Institutional Review Board 23-000931. The trial is registered at ClinicalTrials.gov (National Clinical Trial identifier NCT06216249, first posted January 22, 2024).

## STUDY ENDPOINTS

### Primary Endpoint

The primary endpoint is the 2-y survival rate of patients treated with [^177^Lu]Lu-PSMA-617 on a flexible and extended dosing schedule (investigational arm) in comparison to patients treated with the standard fixed dosing schedule of maximum 6 treatment cycles every 6 wk (control arm). Survival is calculated from the date of the first cycle of [^177^Lu]Lu-PSMA-617 therapy.

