### Secondary Endpoints

The secondary endpoints included the following.
To evaluate the safety of a flexible dosing schedule of [^177^Lu]Lu-PSMA-617 including up to 12 cycles and “treatment holiday” periods by Common Terminology Criteria for Adverse Events guidelines and dosimetry.To determine the overall survival, defined as the time from the date of the first cycle injection of [^177^Lu]Lu-PSMA-617 until death.To determine the PFS defined as the date of the first cycle injection of [^177^Lu]Lu-PSMA-617 to the date of first evidence of progression as defined by either radiographic progression, PSA progression, clinical progression, or death from any cause, whichever occurs first.
a.Radiographic progression is defined as the date of radiographic disease progression on SPECT/CT by visual increase in tumor volume of 30% or greater compared with baseline cycle 1 ± new sites of disease or new sites of PSMA-negative disease progression on CT (10,12) or on PSMA PET/CT as outlined in RECIP or by apparition of new PSMA-negative disease measurable on CT (13). Response assessment criteria using SPECT/CT are summarized in Table 1, and response assessment criteria on PET/CT are summarized in Table 2. See sections 6.8 and 6.9 in the study protocol in the supplemental materials.b.PSA progression is defined as the date when a 25% or greater increase in PSA and an absolute increase of 2 ng/mL or more from the nadir is documented and confirmed by a second consecutive value obtained 3 or more weeks later. Rises in PSA within the first 12 wk will be ignored in the absence of other evidence of disease progression in accordance with the Prostate Cancer Clinical Trials Working Group recommendations. Where no decline from baseline is documented, PSA progression is defined as a 25% increase from the baseline value along with an increase in absolute value of 2 ng/mL or more after 12 wk of treatment.c.Unequivocal clinical progression is defined as follows:

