## STATISTICS AND SAMPLE SIZE DETERMINATION

The primary endpoint of the study is the 2-y survival rate from the date of the first cycle of [^177^Lu]Lu-PSMA-617 therapy. We assumed that the 2-y survival rate in the control group would be 30%. We hypothesized that the 2-y survival rate in the investigational group would be 55%. A 2-sided log-rank test with an overall sample size of 90 subjects (45 in the control group and 45 in the treatment group) achieves 80.3% power at a 0.05 significance level to detect a hazard ratio of 0.50 when the proportion surviving in the control group is 0.30 and the proportion surviving in the treatment group is 0.55 at 24 mo. The study lasts for 48 mo, of which subject accrual (entry) occurs in the first 12 mo.

The accrual pattern across months is uniform (all periods equal). The proportion dropping out or lost to follow-up in the control group and treatment groups is assumed to be around 6 per group during the study period.

This calculation was performed using power analysis and sample size, and the 2-y survival estimates used in the calculation were estimated from the VISION trial data (2).

Randomization is centrally performed in a 1:1 ratio to the 2 treatment arms. The clinical investigators are blinded to the randomization sequence that has been created upfront in collaboration with the local Department of Medicine Statistics using the software application REDCap (Research Electronic Data Capture) (16). On actual sequential allocation of a patient to a treatment arm, both the study team and the patient will be aware of the treatment arm (open label study).

Efficacy will be reported using descriptive statistics by means of number and percentage of patients dead 24 mo after the first cycle (2-y survival rate). Distribution of safety and tolerability results will be compared between both groups using appropriate tests (e.g., χ^2^ tests). Descriptive analyses (median, standard deviation) will be used to determine OS and PFS; group comparisons will be performed using appropriate tests including survival analyses (e.g., Kaplan–Meier estimator). For more details of the statistical analysis plan, see section 10 of the study protocol in the supplemental materials.

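### Survival is counted from the first cycle, not from randomisation, in an open-label trial, so as defined a randomised patient who never starts has no place in the primary comparison

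*Protocol article*

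**What the plan says.** The protocol article fixes the time origin in several places, always in the same way.

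- Primary Endpoint: "The primary endpoint is the 2-y survival rate of patients treated with" the drug on one schedule, compared with the other, and then "Survival is calculated from the date of the first cycle of" the drug. The Abstract agrees.
- Statistics and Sample Size Determination: "The primary endpoint of the study is the 2-y survival rate from the date of the first cycle of" the drug. The descriptive report of efficacy is also a count of deaths at 24 months from the first cycle.
- Secondary Endpoints: overall survival is "defined as the time from the date of the first cycle injection of" the drug until death. Progression-free survival (PFS) starts at the same injection.

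On allocation, the statistics section says "Randomization is centrally performed in a 1:1 ratio to the 2 treatment arms" and that, once a patient is allocated, "both the study team and the patient will be aware of the treatment arm".

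The article does not say that all randomised patients enter the primary comparison. It refers to section 10 of the full protocol for further analysis detail, and that section is not shown.

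**The concern.** Randomisation makes the arms comparable at the moment of allocation. If the clock starts at a later event, the groups compared are those who reached that event. Here the event is the first injection, and both patient and team know the arm while it is still to come. A patient who dies, deteriorates or withdraws in between has no survival time under the stated definition and is not a treated patient.

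If never-starting has nothing to do with arm, the loss costs some precision and does not bias the comparison. If it is related to both arm and prognosis, it moves the 2-year survival difference, and the analysis cannot detect this from treated patients alone. With 45 per arm, each patient is about 2.2 percentage points (1/45), so a handful matters.

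**Working it through.** **Inputs from the article (Statistics and Sample Size Determination).** 45 + 45 patients; 2-year survival 0.30 and 0.55; two-sided log-rank test at 0.05; 12 months' uniform accrual in a 48-month study; about 6 losses per group; stated power 80.3%.

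**Step 1: reproduce the planned power.**
- Exponential hazards are −ln(0.30)/24 = 0.0502 and −ln(0.55)/24 = 0.0249 per month. The hazard ratio is ln 0.55 / ln 0.30 = 0.497.
- Dropout of 6/45 over 48 months gives a rate of −ln(1 − 6/45)/48 = 0.0030 per month.
- Averaging the event probability over follow-up of 36 to 48 months gives 65.5 expected events.
- Schoenfeld: Φ(√65.5 × |ln 0.497| / 2 − 1.96) = 80.9%.

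This agrees with the stated 80.3%. The time origin does not enter the formula, so moving it leaves the planned calculation as it stands.

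**Step 2: selective loss with no true effect.** The number of never-starters is not in the article, so 2, 4 or 6 controls is an assumption. So are their survival (60% or 10%) and a full start in the investigational arm. True 2-year survival is 30% in both arms, which is 13.5 expected survivors of 45.

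Control survival among starters = (13.5 − k·s)/(45 − k), where k controls with 2-year survival s never start. For example, k = 4 and s = 0.60 gives (13.5 − 2.4)/41 = 27.1%, so the apparent gain is 30.0 − 27.1 = 2.9 points.

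The last column is the chance that a pooled two-proportion z-test at two-sided 0.05 wrongly favours the investigational arm (nominal 2.5%): 1 − Φ((1.96·se0 − d)/se1). Here d is the apparent gain, se0 the pooled and se1 the unpooled standard error. For k = 4 and s = 0.60, se0 = 0.0976 and se1 = 0.0974, giving 4.8%.

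| k | s | Control survival in starters | Apparent gain (points) | False win |
|---|---|---|---|---|
| 2 | 0.60 | 28.6% | +1.4 | 3.5% |
| 4 | 0.60 | 27.1% | +2.9 | 4.8% |
| 6 | 0.60 | 25.4% | +4.6 | 6.7% |
| 2 | 0.10 | 30.9% | −0.9 | 2.0% |
| 4 | 0.10 | 32.0% | −2.0 | 1.6% |
| 6 | 0.10 | 33.1% | −3.1 | 1.2% |

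If the lost controls are typical (s = 0.30), the bias is zero for every k. For scale, the standard error of the difference with 45 per arm at 30% is √(2 × 0.21/45) = 9.7 points. The largest figure in the table is about half of that.

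**Step 3: what keeping everyone costs in power.** This uses the 48-month design with no other dropout, and 0, 2, 4 or 6 never-starters.
- Dropped at random from each arm: 82.6%, 80.9%, 79.0%, 77.0%.
- All randomised patients kept, with investigational never-starters surviving like controls (30%): 82.6%, 79.1%, 75.3%, 71.1%.

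Under these assumptions, analysing everyone gives up 1.8 to 5.9 points of power relative to dropping never-starters at random (80.9 − 79.1 and 77.0 − 71.1).

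**The case against.** **No exclusion rule is stated.** The article speaks of 90 randomised patients, the power calculation counts all of them, and the analysis set may be defined in the unseen section 10. This stands as far as it goes: a reader might infer that the plan deliberately excludes untreated patients, and it does not say so. But the time origin is not left to another document. It is stated in the article, and a patient without a first cycle has no value under it.

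**Both arms start alike.** The Investigational Arm Timeline and Control Arm Timeline give the same activity and interval at the outset, and the schedules part only at a response-triggered holiday or after cycle 6. A reader might infer that controls are more likely to leave before cycle 1, because the approved schedule is available outside the trial. The article gives no support for that, and a control who left for the approved schedule would receive the same regimen. Differential non-start may well be small.

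**The worst case is not a forecast.** If six controls never start, survival among the remaining controls could lie anywhere from 7.5/39 = 19.2% to 13.5/39 = 34.6%, and a reader might quote a shift of 11 points. That needs all six to be 2-year survivors in a group with 30% survival, with no loss in the other arm. Nor can the assumed six losses per group be read as never-starters, since they are spread over the study period.

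**The gap is partly bounded.** The Inclusion Criteria require PSMA PET/CT within 8 weeks of the planned first cycle. If randomisation follows confirmed eligibility, the planned gap is within that window. This limits the exposure but does not remove it.

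**Conclusion.** The point holds as a defect in a stated definition. The primary 2-year survival rate and overall survival start at an event after open allocation, and the primary endpoint is worded for treated patients. As defined, never-starters and deaths before cycle 1 fall outside the comparison.

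The size and direction of any bias cannot be determined from the article. The 1.4 to 4.6 points above are an illustration. They rest on 2 to 6 never-starting controls with 60% survival, none lost in the other arm and no true effect. With poor-prognosis losses the sign changes, and with none, or with losses unrelated to prognosis or arm, there is no bias. The stated power reproduces and is not in question here. The reason to act is that the safer definition is cheap, whereas vital status for patients who left before treatment may be hard to recover later. Enrolment has been open since August 2024 (Study Duration).

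**What to change.** 1. Define the 2-year survival rate and overall survival from the date of randomisation, in all randomised patients, by assigned arm. Change the treated-patient wording of the primary endpoint and the first-cycle wording in the Abstract, Secondary Endpoints and statistics section to match.
2. Collect vital status to 24 months after randomisation for patients who never start.
3. Keep the first-cycle origin, in treated patients, as a sensitivity analysis, and report the number of never-starters and the time from randomisation to cycle 1 by arm.
4. For PFS, also start the clock at randomisation, but keep the cycle 1 SPECT/CT as the imaging baseline. The PSA rule for patients without a decline refers to weeks of treatment, so say that this reference is kept. State how never-starters are handled: for example, death or clinical progression counts as an event, and otherwise they are censored.

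**Cost.** Treated patients need no extra follow-up: randomisation precedes cycle 1, so the existing 24-month postinjection visit already falls later than 24 months from randomisation. The added work is vital-status follow-up of the few who never start. The randomisation date should be available from the central REDCap allocation, although the article does not say so. The planned sample size and power formula do not change. If some investigational patients never start, the effect in all randomised patients is somewhat diluted, as step 3 of the working shows. The survival change is a short amendment; the PFS change needs the few extra sentences in item 4.

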### Secondary Endpoints

The secondary endpoints included the following.
To evaluate the safety of a flexible dosing schedule of [^177^Lu]Lu-PSMA-617 including up to 12 cycles and “treatment holiday” periods by Common Terminology Criteria for Adverse Events guidelines and dosimetry.To determine the overall survival, defined as the time from the date of the first cycle injection of [^177^Lu]Lu-PSMA-617 until death.To determine the PFS defined as the date of the first cycle injection of [^177^Lu]Lu-PSMA-617 to the date of first evidence of progression as defined by either radiographic progression, PSA progression, clinical progression, or death from any cause, whichever occurs first.
a.Radiographic progression is defined as the date of radiographic disease progression on SPECT/CT by visual increase in tumor volume of 30% or greater compared with baseline cycle 1 ± new sites of disease or new sites of PSMA-negative disease progression on CT (10,12) or on PSMA PET/CT as outlined in RECIP or by apparition of new PSMA-negative disease measurable on CT (13). Response assessment criteria using SPECT/CT are summarized in Table 1, and response assessment criteria on PET/CT are summarized in Table 2. See sections 6.8 and 6.9 in the study protocol in the supplemental materials.b.PSA progression is defined as the date when a 25% or greater increase in PSA and an absolute increase of 2 ng/mL or more from the nadir is documented and confirmed by a second consecutive value obtained 3 or more weeks later. Rises in PSA within the first 12 wk will be ignored in the absence of other evidence of disease progression in accordance with the Prostate Cancer Clinical Trials Working Group recommendations. Where no decline from baseline is documented, PSA progression is defined as a 25% increase from the baseline value along with an increase in absolute value of 2 ng/mL or more after 12 wk of treatment.c.Unequivocal clinical progression is defined as follows:
i.Marked escalation in cancer-related pain that is assessed by the investigator to indicate the need for other cytotoxic systemic therapy for prostate cancer.ii.Immediate need for initiation of new anticancer treatment, surgical or radiologic intervention for complications due to tumor progression even in the absence of radiologic progression.iii.Marked deterioration in Eastern Cooperative Oncology Group (ECOG) performance status to grade 3 or greater or in the opinion of the investigator ECOG deterioration indicates clinical progression.iv.In the opinion of the investigator, it is in the best interest of the patient to discontinue treatment due to clinical progression.To determine disease control rate defined as the proportion of patients achieving radiographic stable disease (SD), partial response (PR), or CR. CR is defined as absence of a PSMA-avid tumor on either imaging modality. On SPECT/CT, PR is defined as a greater than 30% reduction in visual tumor volume at all sites of involved disease compared with baseline cycle 1, no new sites of PSMA-avid tumor, and no new sites of PSMA-negative tumor on CT; and SD is defined as no change greater than 30% in visual tumor volume compared with baseline cycle 1, no new sites of PSMA-avid tumor, and no new sites of PSMA-negative tumor on CT. Respective response groups on PSMA PET/CT are defined by RECIP (13).To determine disease control rate by combined radiographic plus PSA response with response defined as PSA decline of 50% or more or radiographic PR/CR as defined above.To determine changes in of HRQoL using the following:
a.The Brief Pain Inventory–Short Form. Pain response defined by improvement from baseline (all patients with ≥4/10) of at least 2-point absolute improvement without an overall increase in opiate use.b.Changes in performance status (ECOG).c.The FACT-RNT questionnaire (14).

**TABLE 1. tbl1:** SPECT/CT Response Assessment Criteria

SPECT/CT	CR	PR	SD	PD
Response assessment criteria adopted from Emmett et al. (10)	Absence of any PSMA uptake, no new sites of PSMA-negative tumor	>30% decrease in PSMA-VOL, no new sites of PSMA-positive or PSMA-negative tumor	No change >30% in PSMA-VOL, no new sites of PSMA-positive or PSMA-negative tumor	>30% increase in PSMA-VOL ± new sites of PSMA-positive or PSMA-negative tumor, or new sites of PSMA-negative tumor on CT

SPECT/CT Response Assessment Criteria.

**TABLE 2. tbl2:** PET/CT Response Assessment Criteria

PET/CT	CR	PR	SD	PD
Response assessment criteria adopted from Gafita et al. (RECIP) (13)	Absence of any PSMA uptake, no new sites of PSMA-negative tumor	≥30% decrease in PSMA-VOL without new sites of PSMA-positive or PSMA-negative tumor	<30% decrease in PSMA-VOL ± new sites of PSMA-positive or PSMA-negative tumor *or* <20% increase in PSMA-VOL ± new sites of PSMA-positive or PSMA-negative tumor *or* PR with new lesions *or* PD without new lesions	≥20% increase in PSMA-VOL with new sites of PSMA-positive or PSMA-negative tumor

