## INVESTIGATIONAL ARM TIMELINE

In the investigational arm (*n* = 45), patients will receive intravenous injection of 7.4 GBq (±10%) of [^177^Lu]Lu-PSMA-617 once every 6 wk (±1 wk) for a maximum of 12 cycles until disease progression (except for progression during treatment holiday periods which will lead to treatment continuation) or unacceptable toxicity.

Evaluation of treatment response is performed using posttreatment SPECT/CT and PSA at every cycle. Radiographic response assessment at every cycle uses posttreatment SPECT/CT of cycle 1 as the baseline. If a patient experiences either a PSA decline of 90% or more or a PSA level of less than 1.0 and CR, or a PSA decline of 90% or more or a PSA level of less than 1.0 and PR plus tumor uptake below liver uptake on either SPECT/CT or PET/CT, the subsequent cycle will be postponed until disease progression. The investigational arm is illustrated in Figure 2.

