## STUDY DURATION

Patients may be treated for up to 12 cycles (investigational arm) or 6 cycles (control arm) of [^177^Lu]Lu-PSMA-617 therapy until progressive disease (except for progression during treatment holiday periods in the investigational arm which will lead to treatment continuation), withdrawal of consent, the occurrence of unacceptable toxicity, or a determination by the investigator if the patient is not clinically benefiting.

The duration of subject participation will be from the time of signing informed consent through the 24-mo postinjection visit. The planned duration for the whole study is 48 mo. The study enrollment started in August 2024. Trial completion date is anticipated for December 2028.

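### PFS counts an unblinded decision to discontinue treatment for clinical progression as an event, and that event is possible for up to about twice as long in the investigational arm as in control

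*Protocol article*

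**What the plan says.** Under Secondary Endpoints, PFS runs from the first injection to first evidence of progression "as defined by either radiographic progression, PSA progression, clinical progression, or death from any cause, whichever occurs first". Clinical progression can be met in four ways:

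- Item i: marked worsening of cancer pain that the investigator judges to call for other cytotoxic treatment.
- Item ii: "Immediate need for initiation of new anticancer treatment, surgical or radiologic intervention for complications due to tumor progression".
- Item iii: decline to ECOG grade 3 or worse, or a case where "in the opinion of the investigator ECOG deterioration indicates clinical progression".
- Item iv: "In the opinion of the investigator, it is in the best interest of the patient to discontinue treatment due to clinical progression".

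Statistics and Sample Size Determination states that, once a patient is allocated, "both the study team and the patient will be aware of the treatment arm".

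Treatment length differs by design. Investigational Arm Timeline gives one injection every 6 weeks "for a maximum of 12 cycles until disease progression (except for progression during treatment holiday periods which will lead to treatment continuation". Control Arm Timeline gives the same interval for at most 6 cycles. Study Duration lists, apart from progressive disease and toxicity, a further ground for ending treatment: "a determination by the investigator if the patient is not clinically benefiting".

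**The concern.** Item iv has two weaknesses.

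First, it is circular. Clinical progression is recognised by a decision that is itself taken because of clinical progression. The item sets no threshold, measurement or confirmation, and the person deciding knows the arm.

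Second, a patient can meet it only while there is treatment to discontinue. A control patient who has completed 6 cycles can no longer meet it, whereas an investigational patient in cycles 7 to 12 still can. A patient on holiday has no ongoing treatment to stop, and progression in that period leads to treatment, not away from it.

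The treatment schedule is what the trial randomises, so one component of the endpoint depends on the intervention. Even an impartial investigator would have unequal opportunity to record this event in the two arms. Discretion is a separate matter: an investigator who knows that more cycles are available might call progression sooner or later. At stake is how a PFS difference between the arms can be interpreted.

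**Working it through.** **The plan's own figures.** The article gives no power, event count or assumed median for PFS. Its only power figure, 80.3%, concerns survival. It reproduces closely by Schoenfeld's formula if deaths are counted to month 48. HR = ln 0.55 / ln 0.30 = 0.497. With 65.5 expected deaths (6 of 45 per arm lost over 48 months), power = Φ(√65.5 / 2 × 0.700 − 1.96) = Φ(0.87) = 80.9%. This says nothing about PFS.

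**Which PFS components need ongoing treatment**

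| Component | Requires ongoing treatment? |
|---|---|
| Radiographic progression, PSA progression, death | No |
| Clinical items i, ii, iii | No |
| Clinical item iv | Yes |

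**Window for item iv** (6-week interval in both arms, no holiday)

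- Control: first to last injection 5 × 6 = 30 weeks; to the end of the last interval 6 × 6 = 36 weeks. That is 29% to 35% of a 104-week follow-up.
- Investigational: 11 × 6 = 66 weeks; 12 × 6 = 72 weeks, or 63% to 69%.
- Ratio at most: 72/36 = 2.0 to 66/30 = 2.2.

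**What the window alone could do.** The documents give no rate for item iv, so the following inputs are assumptions. All other PFS components together are exponential with median 6, 9 or 12 months (hazard λ = ln 2 / median), the same in both arms. While on treatment, item iv adds a hazard h equal to 10%, 25% or 50% of λ. It can occur only up to W = 36/4.345 = 8.29 months in control and W = 72/4.345 = 16.57 months in the investigational arm. There are no holidays, and follow-up is 24 months. Simulation of 200,000 patients per arm with no true difference gave:

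| Median of other components (mo) | h/λ | PFS HR, investigational/control | 12-month PFS, control vs investigational |
|---|---|---|---|
| 6 | 10% | 1.02 | 22.6% vs 21.8% |
| 6 | 25% | 1.05 | 19.8% vs 17.6% |
| 6 | 50% | 1.08 | 15.5% vs 12.4% |
| 9 | 10% | 1.03 | 37.4% vs 36.1% |
| 9 | 25% | 1.06 | 34.0% vs 31.4% |
| 9 | 50% | 1.09 | 28.7% vs 25.2% |
| 12 | 10% | 1.03 | 47.7% vs 46.7% |
| 12 | 25% | 1.06 | 44.3% vs 42.1% |
| 12 | 50% | 1.11 | 39.3% vs 35.3% |

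Median PFS differed between arms by about 0.3 months at most.

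Check of the last row by formula, S(12) = exp(−12λ) × exp(−h × min(12, W)), with λ = 0.0578 and h = 0.0289:

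- Control: 0.5 × exp(−0.0289 × 8.29) = 0.394.
- Investigational: 0.5 × exp(−0.0289 × 12) = 0.354.

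**Against sampling error.** If all 90 patients had a PFS event, the standard error of ln HR would be 2/√90 = 0.211. The 95% limits would then lie a factor exp(1.96 × 0.211) = 1.51 either side. The largest illustrated shift, ln 1.11 = 0.104, is about half a standard error.

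**The case against.** The components overlap. A control patient who deteriorates after week 36 is still covered by items i to iii, by PSA and PSMA PET/CT every 12 weeks, and by death. Many patients who meet item iv would soon meet another component, so item iv often changes only the date of the event. PFS is secondary. The window effect runs against the investigational arm, so on its own it would not create a false claim of benefit. All of this stands, and it limits the size. It does not remove the circular wording or the unequal window.

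A reader might infer four stronger things, none of which the document supports.

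- **That PFS is biased.** The document shows that ascertainment can differ. It does not show that it will, or in which direction overall.
- **That any investigator decision to stop is an event.** Item iv covers only stops due to clinical progression. Toxicity and lack of clinical benefit are listed separately under Study Duration.
- **That the opinion clause of item iii has the same fault.** It is subjective, but it has no on-treatment condition and can be met at any time in either arm, including by control patients after cycle 6.
- **That 2 to 5 extra events among 45 patients should be expected.** At an assumed item iv rate of 1% to 2% per cycle, 45 × (0.99⁶ − 0.99¹²) = 2.5 and 45 × (0.98⁶ − 0.98¹²) = 4.5. But this keeps every patient on treatment for 12 cycles. At the control survival rate (exponential), 0.30^(36/104) = 66% are alive at week 36. That alone cuts the figures to about 1.6 and 3.0, before later deaths and before anyone who has progressed or stopped is removed.

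**Conclusion.** The point holds as a risk of differential, unblinded ascertainment in a secondary endpoint. It rests on the wording of item iv, the open-label design and the treatment maxima of 6 and 12 cycles, all stated in the article. The size cannot be derived from the document. On the assumed inputs, the window alone moves the PFS hazard ratio to about 1.02 to 1.11 and lowers 12-month PFS by about 1 to 4 percentage points in the investigational arm, with medians almost unchanged. It works only through patients still event-free and on treatment after about week 36 whose event nothing else catches first. Holidays would alter the windows and were not modelled. Unblinded discretion comes on top, in a direction that cannot be known. The 2-year survival endpoint is untouched. The effect is modest, but the correction is cheap enough to be worth making.

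**What to change.** Under Secondary Endpoints, remove item iv from the PFS event definition and record it instead as a reason for stopping treatment. Study Duration already lists investigator-judged stopping separately, so no clinical decision changes. Retain items i, ii and iii, PSA and radiographic progression, and death, none of which requires ongoing treatment. Continue PSA and PSMA PET/CT every 12 weeks after a stop of this kind until a retained event or the end of follow-up. Report PFS including item iv as a sensitivity analysis. Make the change by dated amendment before PFS is compared between arms.

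Cost: an edit to the definition and one extra analysis. A few events will be counted later or not at all, and some unblinded judgement remains in items i to iii. The 12-weekly assessments are already described for control patients after treatment ends, and for investigational patients during holidays and after cycle 12. They would need to be stated for investigational patients who stop earlier.
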